#### Covariates

Potential covariates for the mother are psychiatric history, ethnicity, level of education, parity, gestational age (duration of pregnancy at study entry), substance use, chronotypes, duration of actual depression and other psychiatric or psychotherapeutic treatment interventions. These factors might affect depressive symptoms during pregnancy. After pregnancy, we will additionally correct for complications during delivery, breastfeeding and objective and subjective sleep parameters, since these factors might influence depressive symptoms after delivery.

Potential covariates for the infant are head circumference, congenital malformations, Apgar-score and neonatal admission at Neonatal Intensive Care Unit.

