## Methods/Design

### Hypotheses

Primary hypothesis: Daily treatment with 6 weeks of morning BLT improves depressive symptoms during pregnancy.

Secondary hypotheses:Clinical improvement of depressive symptoms is accompanied by improved sleep patterns, lower basal cortisol levels and normalized melatonin concentrations during pregnancy.Treatment with BLT during pregnancy improves birth and child outcomes: higher gestational age, higher birth weight, less regulation problems in infants and lower cortisol stress response. In addition, infants will show lower long-term cortisol exposure.

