### Intervention

Participants will be randomly allocated to BLT (9.000 lux) or DRLT (100 lux). Treatment will take place daily at home for 6 weeks, starting at 12–18 weeks pregnancy. Participants will be asked to commence the treatment within 30 min of habitual wake-up time with a duration of 30 min. Participants will sit in front of two light boxes with a distance of approximately 40 cm. The light boxes will be placed in a custom-made scaffolding. In this way, the height of the light boxes can be adjusted per person, ensuring the same distance. Also, the scaffolding ensures lighting from above, which avoids glare [42]. This makes the treatment more comfortable, enhancing treatment adherence.

The active dose was found effective in other studies [23, 41, 42]. Dim red light can be considered to be biologically inactive [55]. Although a Cochrane review of studies in BLT in non-seasonal depression showed that BLT may be effective in as little as 1 week [55], we will choose 6 weeks of daily light exposure, since the 2 studies among pregnant women with non-seasonal depression showed significant effects of BLT from 5 weeks treatment [41, 42].

All participants in both treatment arms will receive treatment as usual. Women are always free to visit their GP, whenever they are in need of this. The GP is always free to start treatment if he/she feels necessary.

When depressive symptoms increase and/or in the case of suicidal ideation, an action plan is set up and appropriate measures will be taken.

Different measures have been taken to enhance treatment adherence:A sensor that measures the amount of lux perceived is installed in the actiwatches, which will monitor the therapy adherence.Since the lamps will be installed into a custom-made scaffolding that ensures lighting from above, treatment will be more comfortable, which enhances treatment adherence.

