### Outcome measures

The primary outcome measure will be the average change in depressive symptoms between the two groups, as measured by the Structured Interview Guide for the Hamilton Depression Scale – Seasonal Affective Disorder version (SIGH-SAD) and the EPDS at different time points. Second, we will study responders vs. non-responders, where response is defined as a ≥50 % decrease to a final score of ≤ 8 on the 17-item Hamilton scale and ≤ 5 on the EPDS.

The secondary outcome measures of this study will be the changes in maternal cortisol and melatonin levels (1), in maternal circadian rhythm (2) and in birth and child outcomes (3).Morning and evening cortisol levels in saliva will be measured as a measure for HPA-axis activity. Morning and evening melatonin levels in saliva will be measured as measure of a participant’s circadian phase position. Outcome measures will be the changes in cortisol and melatonin saliva levels between the two groups.Total 24-h cortisol excretion will be determined from urine. Outcome measure will be the changes in cortisol levels within and between the two groups.Hair will be used as a long-term measure for cortisol excretion. Changes in levels between the two groups will be used as outcome measure.Through actiwatches and a structured questionnaire (the Pittsburgh Sleep Quality Index – PSQI), information will be obtained regarding total sleep time, sleep efficiency and sleep onset latency, as well as circadian estimates from the rest activity rhythm such as intradaily and interdaily variability and rhythm amplitude.Differences in birth and child outcomes between the two groups will be used as outcome measures: pregnancy duration, birth weight, child behaviour, long-term cortisol exposure and cortisol stress response at a routine vaccination.

Finally, we will ask about user expectations and user experiences.

Complete follow-up will be pursued. In case of discontinuing or deviating from the intervention, we will collect outcomes of EPDS and SIGH-SAD assessment.

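### The postpartum maternal analyses are to be corrected for delivery complications, breastfeeding and sleep, all arising after randomisation, so the adjusted postpartum estimates need not be the randomised effect of bright light therapy

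*Protocol article*

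**What the plan says.** The Covariates section first gives potential maternal covariates for symptoms during pregnancy. Most are entry characteristics, but the list ends with other psychiatric or psychotherapeutic treatment and does not say when that is measured. For the period after delivery the wording becomes a commitment: "we will additionally correct for complications during delivery, breastfeeding and objective and subjective sleep parameters". The only reason given is "since these factors might influence depressive symptoms after delivery". For the child: "Potential covariates for the infant are head circumference, congenital malformations, Apgar-score and neonatal admission at Neonatal Intensive Care Unit".

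On timing, the Intervention section states "Treatment will take place daily at home for 6 weeks, starting at 12–18 weeks pregnancy". On the role of sleep, Outcome measures lists it as a secondary outcome ("information will be obtained regarding total sleep time, sleep efficiency and sleep onset latency"), and Hypotheses expects that clinical improvement "is accompanied by improved sleep patterns, lower basal cortisol levels and normalized melatonin concentrations during pregnancy". Hypotheses also states "Treatment with BLT during pregnancy improves birth and child outcomes". The Birth outcomes section, within the infant secondary outcomes, is where delivery complications are collected.

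Two other places limit the point. The General section of the statistical analysis plans a crude primary analysis before an adjusted one. The Primary outcomes section specifies a model with time and treatment only.

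**The concern.** Randomisation protects the comparison of everyone allocated to BLT with everyone allocated to dim red light. Adjusting for variables fixed before allocation keeps that protection. Adjusting for something that allocation may itself have changed does not: it removes the part of the effect that runs through the variable. Where the variable also shares unmeasured causes with mood, it introduces a non-randomised difference between the arms as well. That a factor predicts the outcome, which is the reason the plan gives, is a reason to adjust only for pre-randomisation variables.

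At stake are the adjusted estimates of maternal depressive symptoms at T5, T6 and T7. If BLT improved sleep and this carried over into better mood after birth, the corrected model would understate the benefit that the trial set out to find.

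**Working it through.** **1. Timing.** Treatment starts at 12–18 weeks and lasts 6 weeks, so it ends at 18–24 weeks of pregnancy (12 + 6 and 18 + 6). T3 is 10 weeks later, at 28–34 weeks. Birth is T4, and the postpartum visits are T5 (2 months), T6 (6 months) and T7 (18 months). Delivery complications and breastfeeding can have no baseline value. Sleep has one, but the correction is not limited to it, and Table 1 schedules both actigraphy and PSQI at T5.

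**2. Could allocation change these variables, on the protocol's own account?**

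| Variable | What the protocol says | Firmness |
|---|---|---|
| Sleep | Secondary outcome; expected to improve during pregnancy; Background (BLT and depression) cites better sleep as indirect support for the circadian mechanism said to mediate the effect | Correction is a commitment |
| Delivery complications | Collected under birth outcomes; BLT is expected to improve birth outcomes | Correction is a commitment |
| Breastfeeding | No hypothesis, but it follows randomisation | Correction is a commitment |
| Head circumference, Apgar score, neonatal intensive care | Plausibly downstream of the expected gains in gestational age and birth weight | Potential covariates only |
| Congenital malformations | Unlikely consequence of treatment from 12–18 weeks | Potential covariate only |
| Other psychiatric treatment | May start during the trial: "The GP is always free to start treatment if he/she feels necessary" | Potential covariate; timing not stated |

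**3. Does the plan reproduce a figure here?** No. The documents give no postpartum effect size and no mediated share, so the size can only be illustrated.

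**4. Hypothetical illustration.** Let T be the total effect in SD units and s the share passing through the covariate M. Take T = 0.45, the figure the Background quotes from earlier antenatal trials, purely as a scale. The shares are assumptions.

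Without an unmeasured common cause, adjusted effect = T × (1 − s):
- s = 0: 0.45
- s = 0.25: 0.45 × 0.75 = 0.34
- s = 0.50: 0.45 × 0.50 = 0.23
- s = 0.75: 0.45 × 0.25 = 0.11

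Now add an unmeasured cause with coefficient 0.4 on both M and mood, and a coefficient b = 0.5 from M to mood (all assumed, M scaled to SD 1 within arm). The effect of BLT on M is a = s × 0.45 / 0.5 = 0.9s. Adjustment then removes a further a × 0.4 × 0.4 = 0.144s:
- s = 0: 0.45
- s = 0.25: 0.3375 − 0.036 = 0.30
- s = 0.50: 0.225 − 0.072 = 0.15
- s = 0.75: 0.1125 − 0.108 = 0.00

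A simulation of 2,000,000 participants per scenario gave 0.451, 0.300, 0.155 and 0.004 for this second case. The crude estimate stayed between 0.448 and 0.452 in every scenario.

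**5. What this shows.** If BLT does not change the covariate (s = 0) there is no bias, even with a shared cause. If it does, the estimate is attenuated. If the shared cause acts in opposite directions on M and mood, the extra term changes sign: at s = 0.50 the result is 0.225 + 0.072 = 0.30. In this model the adjusted estimate exceeds the crude one only if that opposing product is larger than b. So attenuation is likely but not guaranteed.

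**The case against.** The best defence is that a valid estimate is already planned. The General section puts the crude primary analysis first and describes adjustment for imbalanced prognostic factors as supplemental, and the primary model contains no covariates. This stands, and it limits the finding to adjusted estimates. It does not rescue them. The Covariates section does not repeat the imbalance condition, and applying it would not help: a difference between arms in postpartum sleep may be the treatment effect itself.

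Four stronger readings are tempting, and the documents do not support them.

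- *The trial has no intention-to-treat estimate.* It does: the crude analysis.
- *The main result or the trial's power is damaged.* The primary hypothesis concerns symptoms during pregnancy, and the firm correction applies only after pregnancy. The end-of-treatment result at T1 is untouched by that sentence. Setting an antenatal effect size and the 63 per arm planned for the treatment course against a postpartum adjustment would say nothing about the trial's main power.
- *The infant analyses are biased.* The infant covariates are only potential. The General section compares variables measured once by unadjusted tests, which covers birth weight, gestational age, MABS, CBCL and infant hair cortisol. The concern applies only where an adjusted infant model is fitted, for instance for the four saliva samples around vaccination.
- *The protocol names postpartum sleep as a mediator.* It does not. Hypotheses says improvement is accompanied by better sleep during pregnancy, and the Background gives sleep only as indirect support. An effect lasting until after birth is plausible from this but not stated.

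The item on other psychiatric treatment is ambiguous: some women enter already treated, and antidepressant use is a stratification factor.

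**Conclusion.** Wrong as written, for the adjusted analyses of maternal depressive symptoms at T5–T7. The plan commits to correcting for variables that follow allocation. One is a trial outcome cited as evidence for the mechanism, and another is collected under the birth outcomes. If BLT changes them, which the protocol's hypotheses make plausible, the adjusted estimates are not the total randomised effect. The direction is probably towards no effect. The size is unknown, and the values of 0.34, 0.23 and 0.11 SD against 0.45 SD are hypothetical because they rest on assumed mediated shares.

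The same concern holds less firmly for head circumference, Apgar score and neonatal intensive care admission in any adjusted infant model, and for other psychiatric treatment if this includes treatment begun after randomisation. It hardly applies to congenital malformations as a consequence of treatment.

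**What to change.** In the Covariates section, state that covariates in treatment-effect models are limited to variables fixed before randomisation. Keep the baseline factors already listed: psychiatric history, ethnicity, education, parity, gestational age at entry, substance use at baseline, chronotype and duration of the current depression. Define other psychiatric treatment as treatment in place at T0.

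Remove delivery complications, breastfeeding, post-baseline sleep and the birth or neonatal variables from these models. Report them as outcomes by arm, or use them only in a separate analysis labelled as exploratory mediation, with its assumptions stated.

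The cost is a change of wording. It needs no new data or visits and leaves the crude primary analysis as it is. It should be made before unblinding.

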## Discussion

We have presented a protocol for an RCT of light therapy for antepartum depression. Two earlier conducted RCT’s have shown the effects of BLT in pregnant women with depression, but studied only a small sample size (*n* = 10 and *n* = 27) [41, 42]. In this trial, we will study the effects of BLT on antepartum depression in a larger sample (*n* = 150) and in addition to the earlier conducted studies, we will not only study the effects of BLT on the mother, but on the infant as well. Moreover, we will study the effects of BLT on maternal endocrine levels and maternal circadian rhythm.

BLT will benefit pregnant women, for they will receive immediate treatment for their depressive symptoms. Psychotherapists are not always available, which would postpone treatment. Also, antidepressant medication is not immediately effective. However, BLT may be effective in as little as 1 week [55]. Moreover, the adverse effects of BLT are mild and short-lived.

The unborn child would benefit from this alternative treatment, for BLT does not cause adverse effects in the unborn child. Also, since BLT may be effective in a short time period, the risks associated with maternal depression (such as lower birth weight) may be diminished.

BLT would benefit society, since BLT has lower costs than treatment with antidepressant medication or psychotherapy.

Finally, since this RCT would be the first to study the effects of BLT in the infant, it would contribute to the understanding of the role of BLT, depression and the maternal HPA-axis in the developing foetus.

Thus, if BLT reduces depressive symptoms in pregnant women, it will provide an alternative, non-pharmalogical treatment for psychotherapy and antidepressant medication in treating antepartum depression. BLT combines direct availability, sufficient efficacy, low costs and high safety, taking the safety for the unborn child into account as well. Moreover, it does not require good language skills and it can be administered at home. These considerations make BLT for treating depression in pregnant women relevant, especially in urban multi-ethnic populations with high prevalence of depression and a low level of personal resources.

## Abbreviations

ACTH: Adrenocorticotrophic hormone
BLT: Bright light therapy
CRF: Adrenocorticotrophic hormone-releasing factor
DLMO: Dim light melatonin onset
DRLT: Dim red light therapy
DSM: Diagnostic and Statistical Manual of mental disorders
EPDS: Edinburgh Postnatal Depression Scale
GP: General practitioner
GR: Glucocorticoid receptor
HAM-D: Hamilton rating scale for depression
HPA: Hypothalamus-pituitary-adrenal gland
MABS: Mother And Baby Scales
MCTQ: Munich Chronotype Questionnaire
PSQI: Pittsburgh Sleep Quality Index
PVN: Paraventricular nucleus
SCID: Structured Clinical Interview for DSM disorders
SIGH-SAD: Structured Interview Guide for the Hamilton depression rating scale - Seasonal Affective Disorder version
